### 2.4. Blinding

Patients and outcome assessors will be blinded throughout the trial. Patients will not be notified until the end of the trial about their group assignment. In addition, using the same guide tubes and turning on the EA apparatus in both groups will help keep the patients blinded during the study. The blinding assessment will be performed at the end of the trial using a Blinding Index (BI) [16]. Patient outcomes will be assessed by an independent study staff, who will assist in filling in the patient-rated questionnaires. Only when serious adverse events are reported can the group allocation be uncovered.

### 2.5. Interventions and Procedures

#### 2.5.1. Treatment Group

The intervention group will receive EA therapy using the following procedures. (a) The patient will be placed in lateral decubitus position. (b) The practitioners will install the guide tubes from the Park sham device at CV2, CV3, CV4, CV6, and bilateral points of SP6 and SP11 (8 acupoints in total). The location of acupoints conforms to World Health Organization guidelines [17]. (c) The verum acupuncture needles (stainless steel, 0.25 mm in diameter and 4.0 mm in length, Dong Bang Acupuncture Inc., Republic of Korea) are inserted at each acupoint through the guide tube to a depth of 10–15 mm. (d) After de qi response is elicited, electrical stimulation is applied for 20 minutes at middle frequency (30 Hz) (STN-111, Stratek, Republic of Korea).

#### 2.5.2. Sham Group

The control group will receive Park sham therapy using the following procedures. (a) The patient will be placed in lateral decubitus position. (b) The practitioners will install the same guide tubes at the same acupoints as in the EA group. (c) Nonpenetrating SA is implemented at each acupoint through the guide tubes. (d) Electrical stimulation is applied for 20 minutes at middle frequency (30 Hz), even though the stimulation is not delivered because the needles have not penetrated the skin.

The treatment session for both groups will be repeated 10 times for 18 days (the visit window is ±3 days). The patients will not take more than one session per day. Acupuncture practitioners with at least 1 year of clinical experience will be involved in the procedures. The practitioners will only explain how many needles will be used, where they are going to place the needles, and how long the needles will remain in place during the session.

The acupoints were selected based on a literature review of Korean acupuncture theories and expert consensus reached after discussion. The selected acupoints are usually used for bladder and genital disorders, including the general symptom of residual urine [18].

#### 2.5.3. Concomitant Medications

According to clinical practice guidelines [19], conventional treatments for stroke and complex management with drugs (antiplatelet agents, anticoagulants, or neuroprotectants), rehabilitation therapies, traditional herbal medications, EA (except for the CV2, CV3, CV4, CV6, SP6, and SP11 acupoints), acupuncture, and moxibustion will be allowed during the study for both groups. In addition, conventional treatments for UI such as oral medications, including diuretics, bladder rehabilitation training, traditional herbal medications, EA (except for the CV2, CV3, CV4, CV6, SP6, and SP11 acupoints), acupuncture, and moxibustion are permitted. However, treatment strategies of fluid therapy and oral administration of any UI drugs should not be changed from 3 days before the trial to the end, because they can significantly affect the symptoms of UI.

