#### 2.2.3. Dropout Criteria

Participants will be dropped out when any one of the following criteria apply: (a) any of the aforementioned exclusion criteria is found after the patient screens in; (b) patients or their legal representatives withdraw consent or want to suspend participation; (c) investigators lose contact with the participant; (d) investigators or patients violate the trial protocol; (e) patients have serious or permanent injury from the trial; (f) patients take any drugs that can affect the results of the trial without direction by the investigators during the trial; or (g) patients have other sufficient reasons to interrupt the trial progress, as determined by investigators' clinical experience.

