## 3. Discussion

This study protocol is intended to conduct a pilot multicentered, randomized, parallel, sham-controlled trial, evaluating the effectiveness and safety of EA, compared with SA, for PSUI patients. The primary effectiveness will be measured by a patient-reported scale, TUFS, with other outcomes, namely, ICIQ-UI-SF, K-IPSS, and LUTS Outcome Score. The safety will be analyzed with adverse events reporting.

According to a review study on acupuncture for voiding disorders after stroke, CV4, SP6, CV3, and CV6 are the 4 acupoints that have been most used in 16 clinical studies [26]. These acupoints are known to control the kidney or body fluid and can possibly manage bladder problems, according to the literature on Korean traditional medicine [18].

Park sham is a placebo acupuncture that was developed to make patients indistinguishable from those who receive genuine needling [27]. With use of a specially developed guide tube, patients cannot observe the needle penetrating through the skin. We will use this guide tube to blind participants, even in the actual EA group. The validation test for SA has already been performed [28].

We designed this trial as a pilot study because no preceding study exists. With the results, we expect to explore more adequate trial settings and calculate statistically powered sample sizes for a full-scale clinical trial to confirm the effectiveness and safety of EA therapies for UI in stroke survivors.

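### The bar on co-treatment at the six trial acupoints covers electroacupuncture only, so manual needling and moxibustion there are open to both arms, sham included

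*Protocol article*

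**What the plan says.** Section 2.5.3 (Concomitant Medications) gives two lists of permitted background care.

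- **Stroke care.** EA appears with an exception for six named acupoints. The list then ends "acupuncture, and moxibustion will be allowed during the study for both groups".
- **Incontinence care.** The same construction returns: "EA (except for the CV2, CV3, CV4, CV6, SP6, and SP11 acupoints), acupuncture, and moxibustion are permitted". No distinction by arm is made.

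The six named points are those of the trial treatment. Section 2.5.1 places the guide tubes "at CV2, CV3, CV4, CV6, and bilateral points of SP6 and SP11 (8 acupoints in total"). In the EA arm, verum needles "are inserted at each acupoint through the guide tube to a depth of" 10–15 mm, followed by de qi and 20 minutes of stimulation at 30 Hz. In the control arm (section 2.5.2) the tubes go on the same points, but "Nonpenetrating SA is implemented at each acupoint through the guide tubes", so no current reaches the patient.

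**The concern.** In both lists the bracket follows EA, and acupuncture and moxibustion come after it as separate items without a qualifier. Read plainly, manual acupuncture and moxibustion at all six trial points are allowed in both arms.

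The sham withholds two things: skin penetration and delivered current. The co-treatment rule protects the second and leaves the first open. A sham patient who has manual acupuncture at, say, CV3 or SP6 as background care receives penetrating needling at a trial point without any breach of protocol.

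At stake is how clean the EA-versus-sham contrast is. Section 3 says the pilot will be used to settle the conditions of a full-scale trial and to size it, so a contrast blurred by co-treatment would carry forward into that planning.

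**Working it through.** **1. Which sites the exception closes.** Section 2.5.1 gives CV2, CV3, CV4 and CV6 on the midline (4 sites) plus SP6 and SP11 on both sides (2 × 2 = 4 sites): 4 + 4 = 8, matching the stated total. Section 2.5.3 names the same six points in 2 of 2 lists.

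| Co-treatment | Trial sites closed | Trial sites left open |
|---|---|---|
| EA | 8 of 8 | 0 of 8 |
| Manual acupuncture | 0 of 8 | 8 of 8 |
| Moxibustion | 0 of 8 | 8 of 8 |

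The argument about penetration concerns the manual acupuncture row. Moxibustion is a separate matter: an active local treatment left open at the same sites.

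**2. Whether another rule closes the gap.**

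- The stability rule at the end of section 2.5.3 covers fluid therapy and oral incontinence drugs only.
- The exclusion criteria (section 2.2.2) do not mention co-treatment at these points.
- Dropout criterion (f) in section 2.2.3 concerns drugs.
- Dropout criterion (d) applies when "investigators or patients violate the trial protocol", but care that follows section 2.5.3 is no violation.
- Dropout criterion (g) could be invoked, but only at the investigator's discretion.

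None of these bars manual acupuncture or moxibustion at the six points.

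**3. Whether such use is plausible.** The protocol's own account of the points suggests it. Section 2.5.2 says: "The selected acupoints are usually used for bladder and genital disorders". Section 3, on acupuncture for voiding disorders after stroke, says: "CV4, SP6, CV3, and CV6 are the 4 acupoints that have been most used in 16 clinical studies". That is 4 of the 6 trial points, or 5 of the 8 sites (CV3, CV4 and CV6, plus SP6 on both sides). The second list in section 2.5.3 permits acupuncture specifically as treatment for incontinence, and one of the two recruiting sites is a Korean medicine hospital. None of this gives a rate.

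**4. Direction and size.** Let Δ be the EA-minus-sham benefit without co-treatment at these points. Let p_E and p_S be the shares of each arm who receive it, and b_E and b_S the benefit it adds in each arm. The observed contrast is then

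Δ + p_E·b_E − p_S·b_S.

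If both arms use it equally often (p_E = p_S = p), the loss is p·(b_S − b_E). It is positive if needling adds more where no penetration has occurred than on top of EA, which is the likelier case. It is zero if b_S = b_E. The documents give none of p_E, p_S, b_E or b_S, so no figure follows.

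**5. Sensitivity of later sizing (assumed values only).** For a two-sided 0.05 test with 80% power, n per arm = 2(1.960 + 0.842)²/d². With an assumed standardised difference d = 0.8, n = 25. If dilution shrank d by an assumed 10%, 25% or 50% (to 0.72, 0.60 or 0.40), n becomes 31, 44 or 99. This shows only how a full-scale calculation responds to a diluted estimate. It says nothing about how much dilution would occur here.

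**6. Effect on the stated sample size.** Section 2.2.4 takes 18 per group with 10% dropout: 18/0.9 = 20 per group, 40 in total, which reproduces. Rewording the co-treatment rule does not enter this calculation.

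**The case against.** The strongest reply is that this is a drafting slip and not a design decision. The only visible reason to name exactly the six trial points is to keep co-treatment off them, and it would be odd to do so while deliberately admitting manual needling. The second list may simply copy the first. That is quite possible, and the text cannot settle intent. It does not remove the point: the rule is stated explicitly, twice, so it is not a detail lost in condensing the protocol, and if the bracket is misplaced the same rewording is needed.

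Second, no consequence is demonstrated. There is no rate of use, no effect size and no bias towards EA, and the site counts describe the rule, not its impact. The evidence that these points are commonly used is indirect, and patients already having ten sessions at them may seldom be needled there again. All of this stands and limits how strongly the point can be put.

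Third, the overlap is partial: manual needling restores penetration but not current, and EA at these points is barred in both arms. That is correct, but penetration is part of what the sham is meant to withhold, and the article gives no reason for protecting only the electrical part.

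Fourth, broad usual care in both arms is a legitimate add-on design. It is, and the proposed change preserves it everywhere except at the trial points.

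**Conclusion.** The concern holds on the text. Followed as written, section 2.5.3 allows manual acupuncture and moxibustion at every trial site in both arms, including penetrating needling in sham patients, and no other section prevents it. The rule does not favour EA. The likely effect is some dilution of the contrast, assuming that such co-treatment is used and that it adds more in sham patients than on top of EA. The documents support neither a rate nor a size, and dilution may be nil. This does not invalidate the pilot. It is a correction that should be made because the gap is explicit, its mechanism is plausible and closing it costs almost nothing.

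**What to change.** In both lists of section 2.5.3, replace the EA, acupuncture and moxibustion items with: *EA, acupuncture and moxibustion (none of these at CV2, CV3, CV4, CV6, SP6 or SP11)*.

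The cost is one wording change in two places and a small restriction on permitted usual care. All three therapies remain available at other points, and the sample size stays at 40. The rewording does not touch co-treatment at other points, which would still be permitted and, because the stability rule covers only fluids and oral incontinence drugs, could still be started or changed during the trial.

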### 2.6. Outcome Assessment

One primary outcome (TUFS) and 3 secondary outcomes (International Consultation on Incontinence Questionnaire for Urinary Incontinence Short Form; ICIQ-UI-SF, K-IPSS, and Lower Urinary Tract Symptoms Outcome Score) will be evaluated for effective assessment.

#### 2.6.1. Primary Outcome

The change in TUFS will be primarily evaluated. PPIUS is a self-rated diary reporting time points, frequency of urination, and the intensity of urine urgency in 24 hours. The patient's perception of intensity is scored from 0 (no urgency) to 4 (urgency incontinence). TUFS is calculated using the sum of the PPIUS scores. This scale has been validated to assess the severity of overactive bladder and Lower Urinary Tract Symptoms, combining the symptoms of urgent and frequent urination [20]. The patient will be asked to report the scale for 24 hours at baseline and at the end of the trial, respectively.

#### 2.6.2. Secondary Outcomes

The change in quality of life for the PSUI between baseline and study closeout will be secondarily evaluated using ICIQ-UI-SF. The questionnaire consists of 3 items, asking (a) the frequencies of UI, (b) the amount of UI, and (c) how strongly the UI affects daily life. The total score will be 0 to 21. The validity and reliability of the scale were analyzed in a preceding study [21].

In the K-IPSS, general symptoms related to the lower urinary tract will also be assessed. The total score (0–35) is calculated for 7 items of 0–5 points each, and the severity will be considered mild (0–7 points), moderate (8–19 points), or severe (20–35 points). The scale includes questions related to prostate symptoms and quality of life [22, 23] and the Korean version of the scale was validated separately [24]. The change in score between the baseline and the study endpoint will be calculated and analyzed.

Finally, the Lower Urinary Tract Symptoms (LUTS) Outcome Score will also be included. This scale can comprehensively evaluate the objective and subjective severity of symptoms. Using the form validated in 2005 [25], we will evaluate the difference in scores before and after the trial.

#### 2.6.3. Safety Assessment

Outcome assessors will investigate any adverse events for safety of EA intervention in PSUI after every treatment session. Investigators will make a decision about the severity (mild, moderate, or severe), seriousness, and causality (definitely related, probably related, possibly related, possibly not related, definitely not related to the intervention, or not assessable) of the reported adverse events.

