## Abstract

This pilot multicentered, randomized, parallel, sham-controlled trial is intended to evaluate the effectiveness and safety of electroacupuncture therapy for poststroke patients with urinary incontinence. Forty stroke survivors aged >19 years will be recruited in 2 hospitals in the Republic of Korea. Patients who experienced stroke within 2 years and satisfy criteria of urinary frequencies ≥2 with either 3 to 4 points on the Patient Perception of Intensity of Urgency Scale or 13 points or more on the Korean version of the International Prostate Symptom Scale (K-IPSS) will be identified, along with other eligibility criteria. Patients will be randomly allocated to either a treatment or control group to receive 10 sessions of electroacupuncture or sham therapies, respectively. Patients and outcome assessors will be blinded. The primary outcome is the change of Total Urgency and Frequency Score between the baseline and the trial endpoint. The K-IPSS, the International Consultation on Incontinence Questionnaire for Urinary Incontinence Short Form, and the Lower Urinary Tract Symptoms Outcome Score will be evaluated for effectiveness assessment. Adverse events will be reported after every session. The Blinding Index will also be calculated. Data will be statistically analyzed with 0.05 significance levels by 2-sided testing.

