#### 2.2.4. Sample Size Calculation

Because there is no preceding study to evaluate the effectiveness of EA for PSUI using the Total Urgency and Frequency Score (TUFS), with a control of any sham devices, we reviewed a statistical study on the appropriate group size for a pilot study. One study suggested that at least 12 participants should be recruited in each group to conduct a pilot trial [14], and another suggested that an increase in size from 12 to 18 or 24 narrowed the confidence interval [15]. Accordingly, we decided that 18 participants per group would be adequate. Therefore, with anticipated dropout rates of 10%, totally 40 participants (20 per group) will be randomized and allocated each EA or sham acupuncture (SA) group.

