### 2.7. Statistical Analysis

Categorical variables will be presented with frequencies and percentage and analyzed by *χ*
^2^ test or Fisher's exact test for demographic information and adverse events. Continuous variables will be presented with mean ± standard deviation and analyzed by two-sample *t*-test or Mann-Whitney *U*-test for demographic information and effectiveness outcomes, depending on the normality of the baseline distribution. If necessary, efficacy data will be evaluated with analysis of covariance (ANCOVA) with covariates of recruiting center and any demographic information, such as gender.

Full analysis set (FAS) (defined as the data set of the participants who receive 7 or more EA or SA sessions and provide the primary outcome at least once) will be primarily used for the effectiveness assessment. Per-protocol (PP) analysis (defined as the data set of the participants who complete every 10 EA or SA session) will be subordinately adopted. Missing data will be imputed by the last observation carried forward method. For the safety assessment, safety set analysis will be performed with the data obtained from all of the participants who receive at least one EA or SA session.

Finally, for the BI assessment, the distribution of actual allocation and participant's responses (EA group, SA group, or DO NOT KNOW) will be presented with 2 × 3 cross tabulation along with the index calculation.

IBM SPSS Statistics for Windows (Version 21.0. IBM Corp. Released 2012. Armonk, NY, USA) will be used, with 0.05 significance levels by a 2-sided test.

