## Figures and Tables

**Table 1 tab1:** Study schedule with enrollment, interventions, and assessment plan.

	Study period												
	Enrollment	Allocation	Postallocation										Closeout
Visits	V1	V2	V3	V4	V5	V6	V7	V8	V9	V10	V11	V12	V13

Time point	Day (−1)	Day 0	Days 1–18 (±3 days)										Day 18 (±3 days)

Enrollment													
Informed consent	X												
*[Demographic information]*	X												
*[Medical history]*	X												
*[Concomitant medication]*	X												
*[Laboratory test* ^*∗*^ *]*	X												
*[Uroflowmetry & bladder scan]*	X												
*[PPIUS]*	X												
*[K-IPSS]*	X												
*[MMSE-K]*	X												
Eligibility screen	X												
Random allocation		X											

Interventions													
*[Treatment: electroacupuncture]*			⧫	⧫	⧫	⧫	⧫	⧫	⧫	⧫	⧫	⧫	
*[Control: sham acupuncture]*			⧫	⧫	⧫	⧫	⧫	⧫	⧫	⧫	⧫	⧫	

Assessments													
*[PPIUS/TUFS]*		X											X
*[ICIQ-UI-SF]*		X											X
*[K-IPSS]*		X											X
*[LOS]*		X											X
*[Blinding Index]*													X
*[Adverse events]*			X	X	X	X	X	X	X	X	X	X	

This table has been modified from the example template recommended by SPIRIT guideline [9].

^*∗*^Blood test: PSA (prostate specific antigen) test for male participants. Urine test: urinalysis and urine culture for all participants, HCG (human chorionic gonadotropin) test for fertile female participants

MMSE-K: the Korean version of Mini-Mental State Examination; PPIUS: Patient Perception of Intensity of Urgency Scale; TUFS: Total Urgency and Frequency Score; ICIQ-UI-SF: International Consultation on Incontinence Questionnaire for Urinary Incontinence Short Form; K-IPSS: The Korean version of International Prostate Symptom Scale; LOS: Lower urinary track system Outcome Score.

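### Adverse event checks are scheduled at the ten treatment visits only; closeout (V13) is blank, so events starting after the session 10 check have no scheduled inquiry

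*Protocol article*

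**What the plan says.** Three places in the protocol article set the timing of adverse event collection, and they agree.

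- Section 2.6.3: "Outcome assessors will investigate any adverse events for safety of EA intervention in PSUI after every treatment session".
- Abstract: "Adverse events will be reported after every session".
- Table 1: the row labelled "Adverse events" is marked at V3 to V12, the same ten visits as the interventions, and is blank at V13.

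V13 is a separate closeout column at Day 18 (±3 days). PPIUS/TUFS, ICIQ-UI-SF, K-IPSS, the LUTS Outcome Score and the Blinding Index are all marked there.

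On the timing of treatment, section 2.5.2 says "The treatment session for both groups will be repeated 10 times for 18 days (the visit window is ±3 days"), and adds "The patients will not take more than one session per day".

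On analysis, section 2.7 says "safety set analysis will be performed with the data obtained from all of the participants who receive at least one EA or SA session". The same section compares adverse events by χ² or Fisher's exact test.

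**The concern.** When checks are tied to sessions, each check can also pick up what has happened since the previous session. A bruise or soreness that appears the day after session 4, for example, can be recorded at session 5. After session 10 there is no next session, and the schedule provides no substitute for it at closeout, where the patient is seen anyway.

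Safety is one of the trial's two stated aims (Background and Discussion), and the pilot is meant to inform a full-scale trial that covers safety as well as effectiveness. A gap at the end of observation would make the late-event count somewhat too low. Needles are inserted only in the EA arm (section 2.5.1) and the sham does not penetrate (section 2.5.2), so any missed event caused by skin penetration would belong to the EA arm.

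**Working it through.** **Is the blank cell real?** The adverse event row of Table 1 has 13 cells, one for each of V1 to V13. The marks fall in cells 3 to 12: 10 marks, none in cell 13. The Blinding Index row, read the same way, has a single mark in cell 13. The blank is therefore not a shifted column.

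**Which intervals are covered?** Number the interval after session k as interval k, with k = 1 to 10.

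- The checks at V4 to V12 follow sessions 2 to 10 and can look back over intervals 1 to 9.
- Interval 10 has no later check.
- Uncovered: 10 − 9 = 1 interval of 10.

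This is only a count. It would become a share of missed delayed events (1/10 = 10%) only if delayed events were equally likely after every session and all showed themselves before the next visit. The document supports neither assumption. It would not be a share of all adverse events, because events apparent at the session itself are checked at all ten visits.

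**How long is the uncovered interval before V13?** Inputs: treatment on Days 1–18 (±3) and closeout on Day 18 (±3), both from Table 1; at most one session a day, from section 2.5.2.

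| Case | Last session | V13 | Interval |
|---|---|---|---|
| Both on the same day | Any day in Day 18 ± 3 | Same day | 0 days |
| Both in the Day 18 window, furthest apart | 18 − 3 = Day 15 | 18 + 3 = Day 21 | 21 − 15 = 6 days |
| Daily sessions from Day 1 (assumption) | Day 10 | Days 15 to 21 | 15 − 10 = 5 to 21 − 10 = 11 days |

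The last row is an extreme. The one-session-a-day limit allows it, but nothing says that sessions will be run that way.

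**What would a check at V13 add?** Scheduled checks per completer rise from 10 (V3 to V12) to 11 (V3 to V13).

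**Effect on the plan's own figure.** Section 2.2.4 says "we decided that 18 participants per group would be adequate" and then "with anticipated dropout rates of 10%, totally 40 participants (20 per group) will be randomized". This reproduces: 18 / (1 − 0.10) = 20 per group, 2 × 20 = 40. The present point does not touch it.

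**The case against.** **The full protocol may define a reporting window or the handling of spontaneous reports, and an article may leave these out.** This stands as far as it goes. Section 2.4 refers to serious adverse events being reported and section 2.2.3(e) to serious or permanent injury, neither tied to a session, so some reporting outside the Table 1 row is presupposed. A reader might infer that events after session 10 are never recorded, and the document does not support that. It supports only the absence of a scheduled inquiry. That absence is not an abridgement, because text, abstract and table all state the same schedule.

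**V13 may coincide with session 10.** This also stands in part. The two share a window, and section 2.6.4 places the blinding question after the final session while Table 1 places it at V13. If both fall on one day, a V13 question adds almost nothing, and later events still go unasked. On the other side, V13 is a separate visit, and the primary outcome is a 24-hour diary at the end of the trial (section 2.6.1). If that diary is meant to follow all ten sessions, V13 would come about a day or more after session 10. That is an inference, not a statement in the document.

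**Both arms follow the same schedule.** This is correct, so there is no procedural imbalance. A reader might infer that the gap mostly understates EA harm. The document gives no event rates by arm, and if equal fractions were missed, the ratio between arms would not change. A greater loss of needle-related events in the EA arm is possible but not shown. Nor does the document support the idea that risk grows over sessions.

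**Conclusion.** The point holds as a minor one. The stated schedule has no adverse event inquiry after the session 10 check, although every completer is due at V13. The uncovered interval before V13 runs from about zero to several days: 0 to 6 if both visits fall in the Day 18 window, and up to 11 only under the assumption of daily sessions from Day 1. How many events would be missed cannot be estimated, and reading one interval in ten as a 10% loss would go beyond the document. The expected consequence is some under-counting of late events in both arms, possibly more of needle-related events under EA. The primary outcome, sample size and error rate are unaffected.

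**What to change.** - In Table 1, mark adverse events at V13.
- In section 2.6.3, extend the timing to read *after every treatment session and at closeout (V13)*, and align the abstract.
- In the safety analysis, include events up to V13.

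The cost is one question at a visit already scheduled, plus small changes of wording. The gain depends on how far V13 falls after session 10: if they are on the same day it is close to nil, and events that start after V13 stay outside the schedule.
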